###### Self-Management Training

As with Stage 1, we are committed in Stage 2, combining improved monitoring with education and support that empowers seniors to proactively prevent transition to CPSP and prevent poor functional recovery. As a team we are experienced in the development/testing of self-management models for people with coronary artery disease [86-88], other forms of chronic illness [89,90], and CPSP [91]. In conjunction with postoperative monitoring and support, participants will engage in SMArTVIEW Restore. Restore is a virtual self-management program, to be delivered in 2-hour sessions weekly, over a 7-week period, from week 0 (week of discharge) to week 6 postoperation (at home).

Figure 2 presents an overview of the Restore curriculum, based on seniors’ CaVS recovery needs identified during patient journey mapping, as well as lessons learned from our previous self-management experience [86-91]. Both content and process elements of Restore are grounded in the fear-avoidance beliefs model [92], which shows how catastrophic pain perceptions can lead to fear, hypervigilance, avoidance, disability, and depression. The curriculum is designed to provide patients with requisite cognitive, emotional, and behavioral skills to manage their postop pain experience in a productive and positive way, leading to optimal functioning. Restore will be run on a time-release basis; interactive features will include weekly recovery goal setting, interactive reflexive activities, wellness journaling, a peer support forum, and a gratitude “wall.”

Both the online interactive elements as well as self-efficacy-enhancing features of Restore will be adapted specifically from the Coventry University Help to Overcome Problems Effectively (HOPE) and Internet-based (iHOPE) programs. As one of the first self-management interventions combining positive psychology and cognitive behavioral therapy theory, iHOPE includes evidence-based and positive psychological activities such as goal setting, action planning, identifying personal strengths, scheduling pleasant activities, mindfulness, relaxation training, and reviewing successes [93]. Feasibility trials have shown that HOPE has the potential to improve important quality-of-life outcomes for people living with and affected by a range of long-term conditions [94,95]. Recently, Coventry University and Macmillan Cancer Support—the United Kingdom’s leading charity and source of cancer support—tested a Web-based version of HOPE (iHOPE) for cancer survivors, comprised of six interactive Web-based sessions, which combine cancer self-management information and education with self-monitoring tools, worksheets, audio- and video-based materials, interactive goal setting and gratitude “walls,” and social networking via email and discussion forums. Feasibility trial results showed that participants’ depression, anxiety, fatigue, fear of cancer returning, positive mental well-being, hope, and gratitude all significantly improved [95]. Participants’ course experience and usability ratings were high, with all of the participants willing to recommend iHOPE to other users [95].

To facilitate our adaptation of iHOPE interactive elements, QoC Health’s Engagement Platform will be leveraged to customize and integrate the validated modules (ie, feature sets) from their existing platforms and to develop customized modules to transform Restore from concept to a codesigned interactive digital solution. QoC will apply the principles of user interface and user experience design to create a user-friendly and intuitive solution with reduced interface friction. An iterative, user-centered design framework featuring participatory design will be used to develop the Web-based solution, which will be optimized for tablet. QoC will facilitate codesign development sessions with our patient representatives to ensure Restore is aligned with their recovery needs and that it considers their technical capabilities (eg, digital literacy and technology-savvy level) and design preferences. The cognitive load on users will be minimized by abating unnecessary decisions/steps and inconsistencies in the interface. To offer the end user an enhanced e-learning experience throughout Restore, the design will feature “digital resting spaces.” This will be achieved by applying the concepts of e-learning (eg, pacing and quantity and diversity of content) and using the principles of white space to balance content and segregate sections.

In summary, our technology partners are cutting-edge eHealth innovators for change with evidence-based solutions. For example, Philips’ IntelliVue Guardian has been shown to significantly increase timely clinical response in hospital, based on abnormal vital signs detection, as well as survival after rapid response treatment [85]. Emerging evidence also suggests that solutions developed through QoC’s Engagement Platform are feasible, acceptable, and beneficial to postop patients and surgical teams [96,97].

**Figure 2 figure2:**
[figure not shown]
The Self-MAnagemenT—VIsion for patient EmpoWerment (SMArTVIEW) Restore curriculum. CaVS: cardiac and vascular surgery.

### Systems Integration

SMArTVIEW deploys a highly integrated “system of systems.” Multiple decentralized and heterogeneous subsystems, with operational and managerial independence, are required to provide our end-to-end SMArTVIEW solution. Our end goal for clinical data management is to ensure that the right information is provided to the right person, at the right time. We have consulted extensively with our information technology and clinical informatics experts to leverage existing assets through systems architecture, as opposed to duplicating functionality or existing data. Moreover, our technology partners’ solutions meet Health Level 7 [98] industry standards for seamless connection and bidirectional data exchange with our hospital information and electronic medical record systems. We will also use application programming interfaces for the extraction of data. We are confident we can achieve integrated exchange of information, from hospital to home.

### Privacy and Data Aggregation

Our additional partners, XAHIVE and mPath, serve as our chief stewards of privacy and data aggregation, respectively. With privacy paramount, we espouse a “privacy by design” approach [99]. Privacy will be role based, highly configurable, and will include the entire circle of care, including formal and informal caregivers and supports by patient consent. To achieve these objectives, we will employ XAHIVE’s secure communication service platform, extensible using a custom off-the-shelf model. The XAHIVE communication protocol does not require servers in order to operate, nor does it require specific hardware devices; these two factors give our team an advantage in the arena of scalability of our deployments. XAHIVE will interface with hospital information systems at both sites—Canada and the United Kingdom—in order to realize (1) consistent security across all communication touch points in the SMArTVIEW system, and (2) a clear chain of custody on the privacy of data per legislative requirements. SMArTVIEW involves multiple “moving parts” that will generate data about recovering seniors’ status and behavior via peripheral devices. Additionally, the solutions we use will generate and aggregate clinical measurements in discrete locations. Third-party data sets (eg, health services utilization data) will also be accessed, allowing for correlations to be made beyond the scope of our integrated systems. There are multiple considerations in the way data is aggregated (eg, efficiency of architecture, reduction of redundancy, and optimization of data accessibility). As leading experts, mPath will govern our data aggregation practices.

### Scalability

With scalability central to our vision, all partner solutions are at technology readiness Level 9, with next to zero time to solution required. Our scalability report will include documentation of (1) unforeseen issues as they arise and problem solving strategies, (2) patient and SVN experience, and (3) results of our comprehensive econometrics evaluation plan, distilled into a projected model of total cost of 1-year SMArTVIEW patient throughput, based on site surgical volumes.

### Evaluation Plan Objectives

The objectives of the evaluation plan are to refine SMArTVIEW (Phase 1) and conduct an RCT to examine its effectiveness.

### Settings

Both evaluation plan phases will take place at Hamilton Health Sciences, Hamilton, Canada, and Liverpool Heart and Chest Hospital, the United Kingdom; the coordinating center is the Population Health Research Institute, Hamilton, Canada.

## Methods

### Phase 1: Usability Testing

#### Participants

Included participants will be (1) aged ≥65 years, (2) undergoing major CaVS with predicted admission >48 hours, and (3) able to read, speak, and understand English such that reflexive intervention surveys generated by eTrAC can be completed (ie, Grade 6 reading level). Those excluded will have planned postop admission or readmission to a nursing home or long-term care facility.

#### Design and Procedures

##### Overview

Rogers’ methods for usability testing [100] will guide SMArTVIEW refinement in the first 9 months. Patients and clinicians will engage in two cycles of focus groups and usability testing at each site, as described in the following sections.

##### Focus Groups

Two focus groups, one at each site, will each be conducted with 5 CaVS patients and 5 SVNs via an adapted semistructured interview guide [101]. With well-established technology partner solutions (ie, applications and devices), our focus is refining overall system intervention flow and staging. After viewing still images of each SMArTVIEW stage, feedback will be elicited about (1) what is seen in each still, (2) expectations for engaging with the SVN and eTrAC solutions at each stage, (3) what each stage should accomplish, and (4) if conceptualization of SMArTVIEW aligns with participants’ mental models of required tasks.

##### Usability Testing

High-fidelity user testing of SMArTVIEW, focused on intraoperability and flow of information, will involve a human factors analyst, a research assistant (RA) with design ethnography training, and the leadership team. Focus group findings will be embedded into test (ie, simulated) clinical scenarios, representing CaVS recovery issues. Using think-aloud [102,103] protocols and task completion checklists, this usability testing cycle—conducted twice, once at each site—will have SVNs and patients rehearse all scenarios wherein information coming from either player can be communicated, via automated monitoring or self-report. Scheduled for 2 hours in the hospital and 2 hours in the patient’s home soon after, but not on the same day, rehearsals will be observed by the human factors analyst and the RA. Through analysis of recorded usability testing data to identify patterns of use, areas of satisfaction or frustration, and system efficiencies and problems, the human factors analyst and the RA will determine actions for system refinement [104,105]. The entire cycle will be repeated, this time observing real-time-based interaction.

### Phase 2: Randomized Controlled Trial

#### Methods

##### Trial Design

Research questions to be addressed in a two-group, parallel-arm RCT (see Figure 3) include effectiveness of the intervention to (1) improve postop pain at 30 days (primary outcome) and (2) composite of major postop complications related to hemodynamic compromise, HQRL, depressive symptoms, health service utilization costs, and patient-level cost of recovery (secondary outcomes).

**Figure 3 figure3:**
[figure not shown]
Randomized controlled trial flow diagram. IWRS: Interactive Web Randomization System.

##### Participants

Participants will be included according to the inclusion/exclusion criteria outlined in Phase 1, with two additional exclusion criteria: (1) participation in Phase 1 and (2) positive Confusion Assessment Method (CAM) screening upon transfer to the surgical ward.

##### The Self-Management—Vision for Patient Empowerment Intervention

The components of the SMArTVIEW intervention will be as described under the Intervention Program, Technologies, and Effectiveness section. The intervention delivery protocol, by stage, is presented in Table 2. This protocol features SVN support from the surgical ward 24 hours/day, 7 days/week.

**Table 2 table2:** SMArTVIEW^a^ intervention delivery protocol by stage.

Stages		Details
**Stage 1: In hospital**		
	**IntelliVue Guardian setup** **(ward day 1)**	
		Upon transfer to the ward, the IntelliVue Guardian early warning system is established by the SVN^b^ on duty, who connects patient to peripheral, cableless devices; establishes baseline/normal vital signs with spot check monitor; activates IntelliVue Guardian; and performs system checks every shift.
		The SVN will receive alerts via mobile device; alerts will be set according to surgeon-sanctioned vital signs parameters programmed into IntelliVue Guardian, which allow for tailoring of profiles for day or night, as well as pre-existing comorbid conditions (eg, atrial fibrillation).
		Upon alerts, SVN assessment, intervention, and escalation of care will be according to usual hospital protocols.
	**Patient and family pain education and hospital-to-home orientation** **(ward day 2)**	
		The SVN will facilitate a 2.5-hour hospital-to-home orientation session implemented at the convenience of the patient, supports (eg, family, friends, and caregivers), and clinical workflow.
		This orientation will focus on the eTrAC^c^ tablet-based applications, the PRAS^d^ educational video, and Restore.
		Following the orientation, the SVN will invite and answer questions.
	**Receipt of SMArTVIEW hospital-to-home package and skills rehearsal** **(day prior to discharge**)	
		On the day prior to discharge, patients will receive their hospital-to-home packages from the SVN, including eTrAC tablet-based solutions, instructions for monitoring vital signs at home, eTrAC 30-day application schedule for monitoring vital signs, SVN video visits, and daily recovery symptom and reflexive surveys.
		Upon receipt of this hospital-to-home package, the SVN will facilitate a 30-minute checklist-oriented rehearsal of all eTrAC features; the SVN will also invite and answer questions.
**Stage 2: In the community**		
	**Setup (week 1 postdischarge)**	
		Philips’ in-home installation team will work with the SVN to establish the Bluetooth-enabled vital signs monitoring system.
		The SVN will then commence monitoring of all incoming data from eTrAC via eCC^e^.
	**Patient monitoring and virtual check-ins** **(first 30 days postdischarge)**	
		The SVN will perform daily 15-minute virtual check-ins—eTrAC video visits—with patients at home from the hospital via eCC, per hospital-to-home package instructions.
		Virtual check-ins will include review of priorities flagged in eCC, review of vital signs and symptom and reflexive survey data, postop pain assessment, and discussion of any patient/SVN concerns.
		Issues identified—via eCC risk stratification or SVN assessment—that require intervention, but are out of the scope of SVN practice, will be escalated to the most responsible clinician.
	**SMArTVIEW-Restore** **(0 to 7 weeks postdischarge)**	
		During recovery, participants will engage the Restore time-release, self-guided, online curriculum (described previously).
		Restore is structured according to seven weekly asynchronous modules, consisting of two to seven activities each.
		Restore is designed to constitute 2-3 hours of online activity, weekly.

^a^SMArTVIEW: Self-MAnagemenT—VIsion for patient EmpoWerment.

^b^SVN: SMArTVIEW Nurse.

^c^eTrAC: Transition to Ambulatory Care.

^d^PRAS: pain relief after surgery.

^e^eCC: eCare Coordinator.

##### Outcome Measures

###### Primary Outcome

The primary outcome is *worst* postop pain intensity upon movement in the previous 24 hours—at 30 days after randomization—averaged across the previous 14 days. This will be assessed using the Brief Pain Inventory-Short Form (BPI-SF), which has well-established reliability and validity in surgical groups, including CaVS [15,106,107]. Common to studies with postop pain as a primary outcome [15,106,107], patients will report *worst* pain-intensity rating both upon rest and movement in the past 24 hours. The primary outcome of worst pain *upon movement* is a more reliable indicator of suboptimal pain management and pain-related interference with recovery-related activities than worst pain *upon rest* [15,106,107].

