###### Secondary Outcomes

####### Postoperative Complications Related to Hemodynamic Compromise

We will capture a composite of complications related to hemodynamic compromise up to 30 days postrandomization, including death, myocardial infarction, and nonfatal stroke. The number of events for the overall composite, as well as number of events per component within the composite, will be reported.

####### All-Cause Mortality and Other Postoperative Complications

All-cause mortality will be captured up to 1 year postrandomization. We will also monitor for new-onset atrial fibrillation and SSI up to 30 days postrandomization.

####### Functional Status

The Short-Form 12 version 2 (SF-12v2) is an established, reliable, and valid tool [108,109] to measure functional status [108,109]. The SF-12v2 provides both physical component summary and mental component summary scores [9,11,46,109].

####### Depressive Symptoms

The five-question version of the Geriatric Depression Scale (GDS-5) will be used to measure depressive symptoms. This tool is a well-validated instrument in the assessment of depression in hospitalized older adults, with high levels of sensitivity and specificity [110,111].

####### Chronic Postsurgical Pain

Development of CPSP is defined [112] as (1) pain that developed after the surgical procedure, (2) being different from pain experienced before surgery, and (3) being present for at least 3 months. Patient responses in the affirmative to each of these questions indicate patients have developed CPSP. For patients who have developed CPSP, pain intensity and related interference with usual daily activities will be measured via the BPI-SF [106,107].

####### Heath Service Utilization-Related Cost

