##### Baseline Measures to Inform Subgroup Analyses

Aside from baseline clinical and demographic information, gender-based pain expectations [118] will be assessed to inform subgroup analyses as evidence suggests that gender-based pain expectations may lead to differences in the experience of pain and related response to interventions [118]. These expectations will be captured using the Gender Role Expectations of Pain (GREP) tool, which captures stereotypic attributions regarding pain endurance, pain sensitivity, and willingness to report pain. The GREP tool has been used in multiple pain investigations [118-123] with acceptable test-retest and internal consistency reliability [118].

Baseline digital literacy will also be assessed using an adapted version of the informational and instrumental support domains of the Patient-Reported Outcomes Measurement Information System (PROMIS) measures. This approach, previously pilot-tested with cardiovascular patients [124], employs five items to examine current level of engagement with mobile and digital technologies.

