#### Feasibility

Our technology partners have contributed equipment and personnel time, in-kind, such that we are able to intervene and follow up on 15 patients at one time per site throughout the study until 30 days follow-up, at which time equipment will be returned to each hospital site for cleaning and reset. Therefore, the RCT (Phase 2) will be executed in five serial, parallel waves of approximately 30 patients per site. In 2014, there were 2311 and 1974 CaVS performed at Hamilton Health Sciences, Canada, and the Liverpool Heart and Chest Hospital, the United Kingdom, respectively. Planned recruitment will occur at a rate feasible for SVN time and access to the surgical populations at both sites. Patients will be enrolled during a 3-week period, with the last week of each recruitment month available for additional patient registrations as needed to accommodate those not meeting postop eligibility. Each site will target recruitment of 14 cardiac and 16 vascular patients during 3 weeks of recruitment—10 patients per week, per site. Allowing for a 25% refusal rate, lost opportunities, and competing studies, this still provides access to 20 patients at Hamilton Health Sciences and 17 patients at the Liverpool Heart and Chest Hospital. Since participant recruitment is only limited by prototype availability, our proposed recruitment target and timeline is feasible and recruitment of 300 participants will be completed in 10 months’ time.

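### No pre-surgery movement-pain score is named at baseline or as a covariate for the primary pain outcome, which costs precision and leaves chance imbalance in prior pain unadjusted in the stated analysis

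*Protocol article*

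**What the plan says.** - **Outcome.** The Primary Outcome section defines worst "postop pain intensity upon movement in the previous 24 hours" from the BPI-SF, "averaged across the previous 14 days". The word for postoperative fixes the timing. The definition mentions neither an incision or graft site nor change from a pre-surgery level.
- **Eligibility.** In Phase 1 the exclusion reads "Those excluded will have planned postop admission or readmission to a nursing home or long-term care facility". The randomized trial reuses those criteria "with two additional exclusion criteria: (1) participation in Phase 1 and (2) positive Confusion Assessment Method (CAM) screening upon transfer to the surgical ward". None of them concerns existing pain.
- **Chronic postsurgical pain.** Under Secondary Outcomes this does separate old from new pain: the pain must have developed after the operation and satisfy "being different from pain experienced before surgery".
- **Baseline.** The section on baseline measures for subgroup analyses opens "Aside from baseline clinical and demographic information, gender-based pain expectations" and goes on to gender-role pain expectations and digital literacy. It names no pain score. The Recruitment section says that baseline data are collected at registration, without a list, and that urgent cases are approached only after surgery.
- **Model.** Primary Analyses specifies a linear mixed model with a prespecified contrast of weekly average worst movement pain. No baseline pain covariate is stated.

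**The concern.** Patients aged 65 or over may arrive with movement pain that has nothing to do with the operation, and nothing in the criteria or the outcome definition sets it aside. A patient's pain level before surgery is a natural predictor of the score reported in the diary afterwards. If it is not measured, or is measured and left out of the model, two things follow:

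1. Variance between patients that could be explained stays in the error term.
2. If one arm happens to contain more patients with prior pain, the estimate moves with that imbalance and the analysis as stated does not correct it.

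The authors recognise the difference between old and new pain, since the chronic pain definition depends on it. That definition would also be easier to apply at the 3- to 12-month interviews with a pre-surgery record to compare against. Timing matters because a pre-surgery score that is not recorded at entry can later be obtained only by longer recall.

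**Working it through.** **Inputs from the Sample Size section:** two-sided alpha .05, SD 20 on a 0-100 scale, difference 10 points, 64 per group per site, and a design effect of 1.5 for the combined 256. **Assumed, because the documents give no figure:** the correlation r between pre-surgery and follow-up movement pain, the baseline SD, and the share p of patients whose worst score comes from pain that the intervention cannot change.

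**1. The plan's own figure.** d = 10/20 = 0.50. The two-sample t-test needs 63.8, so 64 per group (128 per site), and power at 64 is 80.1%. Allowing for 10% loss gives 72 per group (144). For the combined sample, 256/1.5 = 170.7 effective patients, with a detectable difference of 8.63 points (stated as 8.6). The stated sample size reproduces and is not in dispute.

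**2. Gain from a baseline covariate.** Residual SD = 20 × √(1 − r²), with the 10-point effect kept and 64 per group.

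| r | Variance removed (r²) | Residual SD | Power | n per group for 80% |
|---|---|---|---|---|
| 0.2 | 4% | 19.6 | 82% | 62 |
| 0.3 | 9% | 19.1 | 84% | 59 |
| 0.5 | 25% | 17.3 | 90% | 49 |

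**3. Chance imbalance.** The standard error of the between-arm difference in baseline pain is SD × √(2/64). With baseline SD 20 this is 3.5 points, and with SD 30 it is 5.3. If baseline and follow-up SD are both 20, the regression slope equals r. A one-standard-error imbalance then shifts the unadjusted estimate by 0.3 × 3.5 = 1.1 to 0.5 × 3.5 = 1.8 points, against a target of 10.

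**4. Dilution, as an upper-bound illustration.** Suppose the intervention has no effect at all in a share p of patients and the SD stays at 20. The average effect is then 10 × (1 − p).

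| p | Average effect | Power, 64 per group | Power, combined 256 (design effect 1.5) |
|---|---|---|---|
| 0 | 10 | 80% | 90% |
| 10% | 9 | 71% | 83% |
| 20% | 8 | 61% | 74% |

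The objection below explains why these last figures should not be read as the expected loss.

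**The case against.** **The text is silent on baseline pain; it does not deny it.** The baseline section lists extra variables for subgroup analyses and expressly sets aside other clinical data. A condensed article commonly leaves the content of baseline forms and the full covariate list to other documents. This stands. A reader might infer that the final score cannot be adjusted for prior pain, but the article supports only that no baseline pain measure or adjustment is stated.

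**Randomization deals with bias.** This also stands. Prior pain is balanced in expectation, and the two-sided .05 test already allows for chance imbalance on average. What remains is precision, and the shift in the estimate in a trial that happens to be imbalanced. A reading that prior pain biases the comparison is not supported.

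**Total movement pain is a legitimate endpoint.** The Primary Outcome section justifies movement pain by its bearing on pain management and recovery activities, and pain from any source can matter there. A severity score need not attribute its cause in the way a diagnosis of chronic postsurgical pain must, so the two definitions do not contradict each other. Rewording the daily item would depart from an instrument the authors describe as reliable and valid. This stands as a reason to leave the item alone. However, Primary Analyses calls the endpoint acute postoperative pain, so its scope should be stated.

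**The dilution figures are too strong as a forecast.** A reader might infer that power really falls to 71% or 61%. That requires zero effect on non-surgical pain. Yet the education addresses beliefs about analgesics in general, and the self-management programme draws on fear-avoidance, positive psychology and cognitive behavioural methods that are not tied to an incision. Nothing shows that the planned 10 points excludes patients with prior pain. The 10% to 20% share is also assumed.

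**The surgical mix settles nothing.** "Each site will target recruitment of 14 cardiac and 16 vascular patients during 3 weeks of recruitment", so more than half of each wave is vascular. A reader might infer much limb pain before surgery, but the documents report no pre-surgery pain figure. If surgery relieves such pain, r could be lower, which is why the r = 0.2 row is shown.

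**Conclusion.** The point holds as a matter of precision and protection against chance imbalance. The article admits patients regardless of existing pain, scores movement pain without stated surgical attribution, and describes a primary model with no baseline pain term. With r between 0.3 and 0.5, adding that term would remove 9% to 25% of residual variance and lift per-site power from 80% to about 84% to 90%. At r = 0.2 the gain is small (82%). These results assume SD 20, a 10-point effect, 64 per group with complete data, and a correlation the documents do not supply. Per-site power is the relevant scale because the Sample Size section promises adequately powered site-specific analyses.

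The sample size calculation is not wrong, and the trial is not biased by this omission. The change is worth making because it is cheap and the measure has to be collected at entry.

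**What to change.** 1. Add the BPI-SF worst-pain-on-movement item, referring to the period before surgery, to the data collected before randomization. Patients consented preoperatively answer it at registration. Urgent patients answer by recall after surgery.
2. Prespecify that score as a covariate in the primary linear mixed model.
3. Use the same record to support the chronic postsurgical pain criterion that the pain differs from pain before surgery.
4. Leave the daily BPI-SF wording unchanged, and state that the primary endpoint is movement pain from any source.
5. If the full protocol already collects this item, the change reduces to saying so and naming the covariate.

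The cost is one more baseline question and a few lines of text. The downside is recall error in urgent patients, which weakens the covariate for them. If answered before allocation, it does not introduce bias between arms.
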